#### Dose received

Dose received consists of two parts: exposure (i.e. the quantification of components that were actually received) and satisfaction (i.e. how users perceive the intervention). Because the intervention is directly delivered to the participants, exposure to the intervention will be identical to ‘dose delivered’. Consequently, log data of the website and app can be consulted. In order to gain insight into the satisfaction of users with the intervention, a questionnaire regarding appreciation of the intervention and attrition-related factors will be administered at the end of the intervention. The questionnaire about appreciation is based on items from two other questionnaires assessing experiences with e-health interventions [70, 71] and can be found in Table 2. The attrition-related factors will be assessed using questions based on the factors described in an article of Eysenbach [23]. The question about taking part in other programmes targeting a healthy lifestyle is also measured at the follow-up measurement. These questions can be found in Table 3. Furthermore, actual attrition rates will be described and reasons for attrition will be examined. During the study, participants who do not log in for the online sessions, will be contacted and information about the described problems with the website and the app will be kept in a record. At the end of the intervention, the following question will be asked to all users: ‘Did you experience any problems using the mobile application?’. Three response options will be provided: (1) Yes, I could not use the app, (2) Yes, but I could use the app from time to time (3) No, I could use the app without problems. Moreover, participants who discontinue using the intervention will be asked to provide the reasons for dropping out during a telephone call. First they will be asked to freely describe why they stopped using the intervention, afterwards they will be asked to rate possible reasons (i.e. loss of interest in the matter, lack of time, achievement of health norms, loss of motivation for behaviour change, lack of relevant content in the intervention, technical problems and medical or emotional problems) on personal relevance.

**Table 2 Tab2:** Overview of the questions about the appreciation of the website and mobile application

Question	Scale
Appreciation of the website	
Overall, how do you rate the website of ‘MyPlan 2.0’?	1 (very poor) – 10 (outstanding)
How do you rate the quiz?	1–10
How do you rate the questionnaire and the accompanying feedback?	1–10
How do you rate the action planning module?	1–10
How do you rate the coping planning module?	1–10
How do you rate the tips and tricks section?	1–10
How do you rate the feedback in the follow-up sessions?	1–10
Appreciation of the mobile application	
Overall, how do you rate the mobile application of ‘MyPlan 2.0’?	1–10
How do you rate the quizzes?	1–10
How do you rate the monitoring module?	1–10
How do you rate the action planning module?	1–10
How do you rate the coping planning module?	1–10
How do you rate the points collection module?	1–10
Appreciation of ‘MyPlan 2.0’ as a whole	
Was the information and support delivered by ‘MyPlan 2.0’ understandable?	1 (not at all) – 5 (very much)
Was the information and support delivered by ‘MyPlan 2.0’ useful?	1–5
Was the information and support delivered by ‘MyPlan 2.0’ of personal relevance for you?	1–5
Was the information and support delivered by ‘MyPlan 2.0’ motivating?	1–5
Did you enjoy using ‘MyPlan 2.0’?	1–5

**Table 3 Tab3:** Overview of the attrition-related factors from the participants

Question	Scale
‘MyPlan 2.0’ lived up to my expectations	1 (not at all) – 5 (very much)
The website of ‘MyPlan 2.0’ is user friendly	1–5
The mobile application of ‘MyPlan 2.0’ is user friendly	1–5
My GP reacted positively regarding my participation in ‘MyPlan 2.0’	1–5
My friends and family reacted positively about my participation in ‘MyPlan 2.0’	1–5
‘MyPlan 2.0’ helped me to be more physically active/to sit less	1–5
The personal contact with the researchers of ‘MyPlan 2.0’ was an additional reason for me to participate	1–5
Going through ‘MyPlan 2.0’ took a lot of my time	1–5
Filling out the questionnaires took a lot of my time	1–5
^a^I also took part in other programmes targeting my healthy lifestyle (e g. consulting a dietitian, starting to run, …) ^a^Which ones?	Yes/No
While taking part in the study drastic changes in my life occurred (e.g. death of a family member, had a (grand)child, new job, etc.)	1–5
I can work well with a computer	1–5
When I have computer problems, I can rely on others to help me	1–5
I had doubts about participating in this study	1–5

^a^This question is also measured at the follow-up measurement

#### Recruitment and reach

Recruitment and reach refer to the proportion of the target population that participated in the intervention and how the sample was recruited, respectively. Because recruitment of participants will be done via different channels, we will keep track of how many participants were recruited via each channel. This can provide us with insights regarding where and how interventions can be implemented or disseminated.

#### Context

Context discusses possible influences of the environment on intervention implementation and outcomes. The most important influence of context on the implementation of the intervention will be assessed via the short version of the ALPHA questionnaire [66], as mentioned above, and the following question: ‘Did physical or emotional problems prevent you from being more physically active/less sedentary?’

### Data collection procedures

The flowchart of the data collection procedure can be found in Fig. 4. Data collection started in March 2018 and is aimed to finish in April 2019. Participants will be recruited in the city library of Ghent (i.e. ‘De Krook’), in city halls and shopping malls. If a participant is willing to co-operate in the study, they will be offered a tablet and the pre-test measurement will take place. The participant will provide informed consent, choose a behaviour (PA or SB) and complete the questionnaires (see Fig. 3) via an online survey tool (https://www.limesurvey.org/) [72]. Subsequently, researchers will provide instructions on how to download the app. If the participant does not have sufficient time to fill out the questionnaire, they will receive a folder with a link and login code to start/complete the pre-test measurement at home. After completion of the pre-test measurement, the participant will be allocated to one of the eight groups, and will receive an email with the web-link to the appropriate version of the intervention. MyPlan 2.0 and its different conditions can only be accessed via the link sent by the researcher and, later on, via the provided email address of the participant. Participants have no access to the other experimental conditions of MyPlan 2.0. One week after each intervention session, an automatic email to encourage people to start with the following session will be sent. If participants take longer than expected to a complete session, several actions will be taken. Participants who do not start or complete a session after 1 week will be sent an email reminder. When there is no reaction after 2 weeks, participants will receive a telephone call from the researcher. When there is no reaction after 3 weeks, the participant will be considered as a drop-out.

**Fig. 4 Fig4:**
[figure not shown]
Flowchart of data collection

Maximum 1 week after completing the five online intervention sessions, participants will receive an email with the link to the post-intervention measures about PA, SB and determinants of behaviour change (see Fig. 3). The post-intervention measures will also include questions about app usage, intervention appreciation and attrition-related factors, necessary for the process evaluation. One month after intervention completion, participants will again receive an email with a link to the follow-up measures (see Fig. 3).

In order to be able to conduct mediation and moderator analyses and track the change in the determinants of behaviour change, participants will complete the item set regarding the determinants after session 1 and session 3. The link and login will be integrated in the email for sessions 1 and 3.

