### Measurements

To answer our research questions, outcomes will be measured at five time points: 1 week before the intervention (PRE), immediately after session 1 (T1), immediately after session 3 (T2), maximum 1 week after the intervention (POST) and 1 month after the intervention (FU). Figure 3 shows which variables will be measured at each time point.

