### Data management and statistical analysis

Data management and analyses will be monitored and supervised by the team of six researchers and a PhD guidance committee. The data management plan, which describes data storage, management and confidentiality, is provided in Additional file 3. Results of the study will be published anonymously in scientific journals and via public health communication channels. For all publications, the APA guidelines for authorship eligibility will be followed.

Statistical analysis will be performed after data collection is completed. The data of our factorial randomised controlled trial will be analysed using R version 3.2.5 [73].

Descriptive statistics will be provided for the total sample and for all groups. Baseline differences between all groups regarding demographic variables, determinants of behaviour change and the level of PA and SB will be explored by using one-way analysis of variance (ANOVA) (for the continuous variables) and chi-square tests (for the nominal variables). If baseline differences occur in terms of age and gender, they will be included as a covariate factor in the analyses. We will explore the effect of other baseline differences via sensitivity analyses.

To handle our missing data, missing data mechanisms will be investigated. First, we will check whether the missing values are missing completely at random (MCAR) or missing at random (MAR) using the Little Missing Completely At Random test in R [74]. If our data are MCAR or MAR, multiple imputation will be used which provides valid results when the data are at least missing at random [75]. The analysis will be conducted in R using the MICE package [76]. However, one cannot rule out the possibility that the data will be missing not at random (MNAR), therefore sensitivity analyses will also be conducted [75].

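### POST and FU questionnaires are triggered by completing all five sessions, and no route to the primary outcome is described for randomised participants who stop early

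*Protocol article*

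**What the plan says.** Randomisation precedes the first session: "After completion of the pre-test measurement, the participant will be allocated to one of the eight groups" (Data collection procedures). Anyone who later abandons the website is therefore a randomised participant.

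The same section, below Fig. 4, gives the two outcome triggers. For POST: "Maximum 1 week after completing the five online intervention sessions, participants will receive an email with the link to the post-intervention measures". For FU: "One month after intervention completion, participants will again receive an email with a link to the follow-up measures". The Measurements section also times both from the intervention rather than from randomisation.

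Drop-out is defined by use of the programme. After an email reminder at one week and a call at two weeks, "When there is no reaction after 3 weeks, the participant will be considered as a drop-out". Under Dose received, "participants who discontinue using the intervention will be asked to provide the reasons for dropping out during a telephone call"; that contact is described as covering reasons only.

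For missing data (Data management and statistical analysis), "If our data are MCAR or MAR, multiple imputation will be used". The plan adds that one cannot exclude that "the data will be missing not at random (MNAR), therefore sensitivity analyses will also be conducted". The primary analysis is a two-level mixed model on repeated measures.

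**The concern.** The design sets out to isolate the effect of each technique by randomisation. That protection holds for the outcome only if measurement does not depend on something the techniques can change. Completing five sessions is such a thing. The Background warns of a risk that adding techniques makes sessions longer and less engaging. Plan reminders and daily self-monitoring notifications in the app also differ between groups, and could work in either direction.

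If a technique drives away less motivated users, those still measured at that level are a more favourable selection and the technique looks better than it is. If it retains them, it looks worse. The Discussion mentions unequal attrition only as a source of unequal group sizes, not of bias. No later analysis can recover outcomes that were never requested.

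**Working it through.** **1. The plan's own attrition figure.** Inputs from Participants: 260 needed, about 480 recruited, 46% attrition tolerated. 1 − 260/480 = 45.8%, which rounds to 46%. In reverse, 260/(1 − 0.46) = 481.5, so 482 against about 480. The figure reproduces.

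**2. Tracing a participant who stops after, say, session 2.**
- PRE is complete and a group has been allocated.
- The item set on determinants may be complete at T1.
- Reminder, call, then drop-out status after three weeks without reaction.
- A telephone conversation about reasons.
- POST: the described trigger, five completed sessions, is never met.
- FU: the described trigger, one month after completion, is never met.

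So no post-baseline measurement of the primary outcome is described for this person.

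**3. How many could be affected.** At the tolerated attrition, 480 − 260 = 220, which leaves 260/8 = 32.5 measured per group of 60. This is an upper figure for that attrition rate, because it treats all loss as programme non-completion. At the 60–80% that the Background reports for earlier interventions it would be 480 × 0.60 = 288 to 480 × 0.80 = 384.

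**4. Illustration of possible bias.** Nothing in this step except the 46% and the 0.19 comes from the plan. Assume that staying and the outcome share a latent correlation r, that a proportion p is retained at each level of a technique, and that mean retention is 54%. With z the normal point having upper-tail area p, the retained group's mean is shifted by r × φ(z)/p. The bias in an unadjusted completers' contrast is r × [φ(z₁)/p₁ − φ(z₀)/p₀].

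| p | φ(z) | φ(z)/p |
|---|---|---|
| 0.44 | 0.3944 | 0.8964 |
| 0.49 | 0.3988 | 0.8139 |
| 0.59 | 0.3887 | 0.6589 |
| 0.64 | 0.3741 | 0.5846 |

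| Retention at the two levels | Difference in φ(z)/p | r = 0.1 | r = 0.3 | r = 0.5 |
|---|---|---|---|---|
| 54% v 54% | 0 | 0 | 0 | 0 |
| 49% v 59% | 0.155 | 0.016 SD | 0.047 SD | 0.078 SD |
| 44% v 64% | 0.312 | 0.031 SD | 0.094 SD | 0.156 SD |

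The non-zero entries span 8% to 82% of 0.19, if that target is read as a standardised mean difference; the article does not state its metric.

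**5. What the planned imputation has to work with.** PRE exists for everyone. Determinants at T1 and T2, weekly goal attainment and log data exist for some who stop later. None of these is physical activity or sedentary time after stopping. With no observed POST or FU value in any non-completer, the imputation model carries completers' outcomes over to non-completers with similar earlier data. Little's test can reject MCAR, but it cannot distinguish MAR from MNAR.

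**The case against.** The strongest reply is that the plan nowhere specifies a completers-only analysis. Multiple imputation, MNAR sensitivity analyses and a mixed model can all keep every randomised participant in the comparison. That stands. A reader might infer that the factorial comparison turns into a comparison of completers; the documents do not support this for the analysis set. It is true only of the observed outcomes.

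Second, the article does not say in so many words that questionnaires are withheld from drop-outs. The absence of a route is inferred from the only trigger described, and the flowchart (Fig. 4) and measurement schedule (Fig. 3) are not shown. This also stands, and it limits certainty.

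Third, a reader might take 220 as the number without outcomes by design. But 46% is a tolerated loss, not a forecast, and it also covers completers who ignore the questionnaire, whom the trigger does not affect. The article gives reasons for expecting less attrition than in earlier programmes.

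Fourth, the bias figures rest on an assumed correlation and assumed retention gaps, and they ignore baseline adjustment and imputation. They show that the order of magnitude can matter beside a small target effect; they do not predict the trial's bias. The Background speaks of a risk, so differential completion is plausible, not documented, and its direction is unknown.

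Fifth, a reader might infer that session 1 to session 5 can stretch to 16 weeks. That takes four gaps of about four weeks, with the three-week clock starting at the invitation email. If it starts at the previous session, the figure is about 12 weeks. The article does not settle which, so no firm ceiling follows.

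Finally, timing POST from the end of a self-paced programme is a defensible choice for completers. Moving them to fixed times would be a trade-off, and the remedy does not need it.

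**Conclusion.** The point holds in limited form. As the article describes it, measurement of the primary outcome after baseline is conditional on a post-randomisation behaviour that the tested techniques may influence, and participants who stop have no described route to it. The as-randomised estimate therefore depends on an unverifiable extrapolation from completers, which the MNAR analyses can probe but not replace with data. Up to about 220 of 480 are exposed if all tolerated attrition is non-completion. The illustrative bias is about 0.02 to 0.16 SD under the assumptions shown, and zero with equal retention. The conclusion rests on the prose alone; if Fig. 3 or Fig. 4 shows outcome collection from drop-outs, the text needs only to say so.

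**What to change.** Send the POST and FU questionnaires to every randomised participant, whatever their use of the programme. Completers can keep the present timing. For those who have not finished five sessions, use a fixed time from randomisation, for example the nominal end of the programme or the moment drop-out is declared, with FU one month later. Offer the questionnaire through the reminder email and telephone call already in place. Record stopping the intervention and withdrawing from measurement as separate events. Include the outcomes obtained in this way in the planned as-randomised mixed model and imputation, so that non-completers contribute observed values.

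The cost is a changed email trigger, a few more emails and one paragraph of protocol text. The drawback is that outcome timing will differ somewhat between completers and non-completers.

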### Data management and statistical analysis

Data management and analyses will be monitored and supervised by the team of six researchers and a PhD guidance committee. The data management plan, which describes data storage, management and confidentiality, is provided in Additional file 3. Results of the study will be published anonymously in scientific journals and via public health communication channels. For all publications, the APA guidelines for authorship eligibility will be followed.

Statistical analysis will be performed after data collection is completed. The data of our factorial randomised controlled trial will be analysed using R version 3.2.5 [73].

Descriptive statistics will be provided for the total sample and for all groups. Baseline differences between all groups regarding demographic variables, determinants of behaviour change and the level of PA and SB will be explored by using one-way analysis of variance (ANOVA) (for the continuous variables) and chi-square tests (for the nominal variables). If baseline differences occur in terms of age and gender, they will be included as a covariate factor in the analyses. We will explore the effect of other baseline differences via sensitivity analyses.

To handle our missing data, missing data mechanisms will be investigated. First, we will check whether the missing values are missing completely at random (MCAR) or missing at random (MAR) using the Little Missing Completely At Random test in R [74]. If our data are MCAR or MAR, multiple imputation will be used which provides valid results when the data are at least missing at random [75]. The analysis will be conducted in R using the MICE package [76]. However, one cannot rule out the possibility that the data will be missing not at random (MNAR), therefore sensitivity analyses will also be conducted [75].

To evaluate the primary aim of the intervention, PA and SB will be analysed in one statistical analysis. The scores of PA and SB will be standardised (z-score) in order to obtain a common metric. For PA, the mean and SD of the population will be based on self-report IPAQ data self-report IPAQ data from Belgian adults (m_totalPA_ = 831.5 min/week, SD_totalPA_ = 579.8; m_MVPA_ = 459.9 min/week, SD_MVPA_ = 407.2 min/week) [77]. For SB, the mean and standard deviation of the population will be based on self-report SIT-Q-7d data from Belgian adults (m_totalSB_ = 9,57 h/day, SD_totalSB_ = 3,20 h/day) [78]. The z-scores for SB will be multiplied by − 1. That way the amount of healthy behaviour is reflected in positive scores. Mixed models (two levels: repeated measures clustered within participants) will be performed using the ‘lme4-package’ [79] to investigate the effect of the (combination) of the three behaviour-change techniques (i.e. action planning, coping planning and self-monitoring) on behaviour change [80]. The participants’ choice of target behaviour (i.e. PA or SB) will be included in the analysis as a moderator. Furthermore, to evaluate our secondary outcome, logistic regression analyses will be used to investigate whether the process on goal achievement has an influence on the primary outcome.

To evaluate the secondary aim of the intervention, PA and SB will be analysed both together for analysing the mediating effect of personal determinants. This because all participants filled out one version of the personal determinants (i.e. the version focussing on PA or the version focussing on SB). These outcome variables will be considered as personal determinants regarding the chosen health behaviour rather than personal determinants regarding increasing PA or decreasing SB. Mediating effects of the personal determinants of behaviour will be investigated using structural equation modelling [81]. Next, moderating effects of demographic variables will be identified via interaction terms by including them as an extra between factor in the analyses.

To evaluate the third aim of the intervention, three groups of participants will be identified based on their ‘mindset’ regarding behaviour change: ‘pre-intenders’, ‘intenders’ and ‘actors’. This will be based on their answer on the personal determinant ‘intention to change’. The moderating effect will be identified via interaction terms by also including them as an extra between factor in the analyses.

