### Participants

This study targets adults in the general Belgian population. The following inclusion criteria will be taken into account: (1) being ≥ 18 years old, (2) Dutch-speaking, (3) having Internet access and (4) being the owner of a smartphone. Before entering the study, people have to complete the ‘Physical Activity Readiness Questionnaire’ (PAR-Q) [57] which is a screening instrument to detect individuals at risk for adverse effects when being more physically active. The PAR-Q is a self-report instrument consisting of seven items to be answered by ‘yes’ or ‘no’. Participants will be excluded when one item or more will be endorsed. Participants receiving concomitant care or other interventions will not be excluded.

A convenience sample will be attained by recruiting possible participants in the city library of Ghent (i.e. ‘De Krook’), in city halls and shopping malls. Also participants will be recruited by social media, contacting participants of previous studies who indicated as having interest in other research, recruiting acquaintances and students, and applying snowball sampling.

Based on the meta-analysis of Conn et al. (2011) [58], we would like to be able to observe a small effect size of 0.19. To detect within- and between-subjects effects under significance level alpha = 0.05, and with a power of 0.80, a sample of 260 participants is needed. However, we will aim to recruit approximately 480 participants to take attrition into account. As such, an attrition rate of 46% of the participants is acceptable within this study, which seams feasible to the researchers. This is because actions to decrease drop-out were taken; no extensive questionnaires were used in MyPlan 2.0 in contrast to previous research (e.g. MyPlan 1.0) and, furthermore, the programme was adapted to increase user engagement based on both qualitative and quantitative research [46, 47].

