The participants will be randomly allocated to eight equal groups (60 participants within one group). The randomisation will be done by the author of this study. Before recruitment of participants, blocked randomisation will be used to form an allocation list for the eight different groups. A computer random number generator (http://www.randomization.com) [59] with a block size of 40 will be used to assign the group numbers in random order within each block. The allocation list will be concealed for the researcher during the recruitment of participants. Each time a participant completes a pre-test measurement (at the library, city hall, shopping mall or at home; see Fig. 4) an automatic email will be sent to the researcher. After receiving this email, the participant will be allocated to the next number on the allocation list and will consequently be assigned to a group. By doing this, the allocation will be concealed until participants are enrolled and assigned to the intervention [60]. After assignment, the researcher will not be blind for the allocated intervention: the researcher will send participants different website links to their corresponding intervention. The participants on the other hand will not be aware of the different conditions of the study: they will only receive one website link (corresponding with their intervention).

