Participants will also complete questions regarding demographic information (age, sex, educational level, occupation, marital status, height and weight) and intervention usage (see ‘Process evaluation’). Furthermore, the short version of the ‘Instruments for Assessing Levels of Physical Activity and fitness’ (ALPHA) questionnaire [66] will be administered, which measures the perceptions of the physical environment (e.g. Are there many shops within easy walking distance of your home?). This questionnaire shows good reliability and predictive validity [66].

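### Age and gender become covariates only if baseline tests show a difference, so the primary model is chosen on chance imbalance instead of prognosis; the cost in precision is probably small

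*Protocol article*

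**What the plan says.** Under Data management and statistical analysis, the protocol article compares all groups at baseline on demographics, determinants, physical activity and sedentary behaviour. These differences "will be explored by using one-way analysis of variance (ANOVA) (for the continuous variables) and chi-square tests (for the nominal variables"). The next two sentences give the consequences: "If baseline differences occur in terms of age and gender, they will be included as a covariate factor in the analyses", and "We will explore the effect of other baseline differences via sensitivity analyses". No threshold for a difference is given, and it is not said whether a difference in one of the two variables brings in one or both.

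The same section describes the primary analysis: "Mixed models (two levels: repeated measures clustered within participants) will be performed using the" lme4 package, with chosen target behaviour as a moderator. Age and gender are not named there as covariates, and the time and baseline terms are not spelled out.

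Under Participants: "The participants will be randomly allocated to eight equal groups (60 participants within one group"), from a blocked list prepared before recruitment. Allocation follows completion of the pre-test. Age and sex are on record for everyone (Measurements): "Participants will also complete questions regarding demographic information (age, sex, educational level, occupation, marital status, height and weight").

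**The concern.** In the set of people randomised, a baseline difference between groups can only be chance. The ANOVA and chi-square tests therefore examine a null hypothesis known to be true, and their result says nothing about whether adjustment would help. That depends on how strongly age and gender predict the outcome.

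The test is also poorly aimed. It is an omnibus comparison of eight groups, whereas the Discussion says that main effects and two-way interactions are of most interest. A main effect compares four groups with the other four. The omnibus test can miss imbalance on that contrast, or flag imbalance that is irrelevant to it.

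At stake are a primary model fixed only after the data are seen, under a rule that two analysts could apply differently, and whatever precision the two covariates could have given.

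**Working it through.** **Inputs from the article.** Eight groups of 60, so 8 × 60 = 480 recruited; 260 needed; 46% attrition acceptable. These agree: 260/(1 − 0.46) = 482 and 1 − 260/480 = 45.8%. The plan gives no figure for the covariate rule, so there is none to reproduce.

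**Assumptions, not in the article.** Test level 0.05. Age and gender together explain a share R² of outcome variance, taken as 0.02 to 0.10, with 0.20 as an extreme. Repeated measures correlate at rho between 0.4 and 0.7.

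**Step 1: how often the rule acts.** Under randomisation each test flags with probability 0.05. At least one flags with probability 1 − 0.95² = 0.0975 (9.2–9.8% in simulation of the eight-group factorial). Neither flags with probability 0.95² = 0.9025.

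**Step 2: value of the covariates for a single post score.** The standard error is multiplied by √(1 − R²).

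| R² | Multiplier | Fall in SE |
|---|---|---|
| 0.02 | 0.990 | 1.0% |
| 0.05 | 0.975 | 2.5% |
| 0.10 | 0.949 | 5.1% |
| 0.20 | 0.894 | 10.6% |

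**Step 3: how much of this the rule recovers.** In simulation at N = 480 and R² = 0.10, the standard error was 0.0913 without adjustment, 0.0911 under the conditional rule and 0.0868 with adjustment always. The rule recovers almost nothing. Its type I error was 0.047–0.055.

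**Step 4: value for a technique-by-time contrast.** Generalised least squares with PRE, POST and FU, total variance 1, rho = 0.5, and covariates explaining only between-person variance:

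| Setting | SE, R² = 0 | SE, R² = 0.10 | Fall |
|---|---|---|---|
| PRE means free, N = 480, complete | 0.0913 | 0.0913 | 0 |
| PRE means free, N = 480, 46% with PRE only | 0.1169 | 0.1160 | 0.8% |
| PRE means equal, N = 480, complete | 0.0791 | 0.0776 | 1.9% |
| PRE means equal, N = 480, 46% with PRE only | 0.1076 | 0.1056 | 1.9% |

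**Step 5: using the PRE outcome.** This is separate from age and gender. With PRE means free and complete data, the contrast reduces to a change score, with variance proportional to 2(1 − rho). Adjusting for PRE gives 1 − rho². The ratio is (1 − rho²)/(2(1 − rho)) = (1 + rho)/2, so the reduction is (1 − rho)/2: 30%, 25% and 15% at rho = 0.4, 0.5 and 0.7.

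Dropout shrinks this, because a mixed model with free PRE means already uses participants who have PRE data only. At 46% dropout the constrained-to-free variance ratio is (0.1076/0.1169)² = 0.847 at rho = 0.5 and (0.0887/0.0928)² = 0.914 at rho = 0.7. The reductions are then about 15% and 9%.

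**The case against.** The best defence is that the rule is narrow and nearly harmless. Only two variables, both named in advance, can enter; other baseline differences go to sensitivity analyses. Type I error stays near nominal. Demographics also enter without any test in the secondary-aim analyses, where "moderating effects of demographic variables will be identified via interaction terms by including them as an extra between factor in the analyses". All of this stands and limits the size of the point. It does not justify the rule for the primary analysis.

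Stronger readings are tempting, but the document does not support them:

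- **A large power loss.** Reading "we would like to be able to observe a small effect size of 0.19" as a standardised mean difference, with N = 260 and rho = 0.5, using the PRE outcome raises power from about 33% to 42%. A reader might charge that gain to the covariate rule. It comes entirely from Step 5. It also needs free PRE means, which the article does not state, and a metric that it does not give. Read as Cohen's f (a mean difference of 0.38), a two-group main effect needs only 218–220 participants, so this point gives no ground for calling the trial short of power.
- **Ignoring the PRE outcome.** The article does not list its fixed effects, and an article may leave these to the fuller plan. Silence here is not an error.
- **Many false baseline differences.** Eighteen independent tests would give at least one in 1 − 0.95¹⁸ = 60% of trials. But the variables are not independent, and all except age and gender reach only sensitivity analyses.
- **Invalid standard errors.** The simulated type I error shows no distortion of note.

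**Conclusion.** The point holds in a limited form. The article states a rule that picks covariates on chance imbalance, gives no threshold for it, and so leaves the content of the primary model to be settled by the data. The main argument is prespecification; lost precision is secondary.

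The figure of about 90% for trials using neither covariate rests on the assumed 0.05 level and on treating the two tests as independent. The precision cost of about 0–2% of the standard error (technique-by-time contrast) or 1–5% (single post score) rests on an assumed R² of at most 0.10. The article gives no value for R², so the cost could be larger if age and gender predict the outcome more strongly.

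The benefit from the PRE outcome could be more substantial, but it is conditional on the model otherwise leaving PRE means free. It belongs with the remedy and is not a fault found in the text.

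**What to change.** Replace the two sentences on baseline differences with wording to this effect: baseline characteristics are tabulated by group without significance tests as a basis for model choice, and the primary mixed model includes age and gender as covariates whatever their distribution across groups. Any further covariates for sensitivity analyses should be named in advance for their expected relation to the outcome.

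State also how the PRE outcome is used. One option is to constrain the PRE mean to be equal across randomised groups within chosen behaviour, with technique terms only at POST and FU. The other is to adjust for the PRE z-score. The two are close with complete data but differ under dropout, because the constrained model keeps participants who have PRE data only. Chosen behaviour is already in the primary analysis as a moderator and needs no addition.

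All the variables are already collected at PRE, so the cost is analysis wording only. The change should be recorded where the article says protocol modifications will be reported, before outcomes are examined by group.
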